## Introduction

Over the last thirty years, nutrition in the intensive care unit (ICU) has evolved from supportive therapy to an active treatment that can attenuate the harms of critical illness [1]. Early nutrition, delivered enterally, has become the standard of care for most critically ill patients and is recommended by the major organizations for clinical nutrition and critical care [1–4]. Enteral nutrition (EN) offers many physiological benefits throughout the gastrointestinal (GI) tract, including maintenance of intraepithelial junctions, mucosal lymphoid tissues, and villous height and lower infection risk by preventing bacterial translocation [5]. Furthermore, clinical studies have demonstrated a benefit with a recent meta-analysis by the European Society of Intensive Medicine (12 randomized controlled trials (RCTs), 597 patients) demonstrating a reduction in infectious morbidity when EN was delivered within 48 hours of ICU admission [3]. Another meta-analysis, including 6 RCTs and 5025 critically ill patients, showed a reduction in mortality with early EN compared to parenteral nutrition (PN) [4]. Despite this and guidelines recommending early initiation of EN, malnutrition in ICUs continues to be a problem with 56–68% of patients in Canadian ICUs being underfed relative to their calculated caloric requirements [6].

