### Participants

We will include all patients 18 years of age or older admitted to the ICU for at least 24 hours who have a prescription for EN or are receiving NIPPV for greater than 48 hours. Patients who received majority NIPPV for 48 hours at any one time will also be included even if they were not prescribed EN. EPIC Hyperspace is now the Electronic Medical Record (EMR) used in hospitals in Hamilton. We will include patients admitted to the ICU since EPIC went live at each site. For St. Joseph’s Hospital Hamilton (SJHH) this is between January 1, 2018, and December 31, 2023. For the two sites at Hamilton Health Sciences (HHS), this is between June 4, 2022, and December 31, 2023. Exclusion criteria includes patients receiving only nocturnal NIPPV, patients who have had gastrointestinal surgery in the month preceding ICU admission, and patients who have confirmed or suspected luminal obstruction on admission. For the purposes of this study NIPPV will exclude high flow nasal canula (HFNC).

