To determine risk factors associated with diarrhea during ICU admission	**Dependent Variable** WHO-defined diarrhea	Age, sex, type of nutrition (IEN/CEN), antibiotics, GI comorbidities, vasopressor/inotropes, daily caloric intake, NIPPV, surgical/trauma/medical admission	Logistic Regression
Secondary Outcomes			
**Research Objectives**	**Outcome**	**Covariates/Subgroups**	**Analytical Approach**
To determine whether IEN or CEN is better for reaching caloric requirements during ICU stay	**Dependent Variables:** Average caloric intake (percent goal determined by RD or 25 kcal/kg) at 48 hours and 7 days after initiation of CEN/IEN Proportion of patients on PN at 48 hours and 7 days after initiation of CEN/IEN	NIPPV, Age, sex, antibiotics, GI comorbidities, type of nutrition (IEN/CEN) vasopressor/inotropes, daily caloric intake, surgical/trauma/medical admission	Descriptive statistics (average caloric intake) and corresponding 95% CI Descriptive statistics (proportion of patients on PN) and corresponding 95% CI Logistic regression
To determine whether IEN or CEN is associated with ICU-acquired bloodstream infection or *Clostridium difficile* infection	Incidence of positive blood cultures drawn at least 48 hours after admission, excluding coagulase-negative staphylococcus unless suspected by ICU team to not be contaminant.	NA	The incidence of bloodstream infections will be computed as the number of new cases during ICU stay divided by the person-time at risk. Descriptive statistics (proportion of patients with ICU-acquired bloodstream infection or *C. difficile infection*) and corresponding 95% CI
To determine whether IEN or CEN is associated with differences in mortality or length of stay (ICU or hospital)	**Dependent Variables** Mortality (ICU and hospital) Length of stay (ICU and hospital)	Age, sex, type of nutrition (IEN/CEN), antibiotics, GI comorbidities, vasopressor/inotropes, daily caloric intake, NIPPV, surgical/trauma/medical admission	Descriptive statistics (mortality and length of stay) and corresponding 95% CI Logistic regression

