### Pilot testing

We will begin with an iterative process of 40 randomly selected patients, 20 from each site. This will allow us to review and refine the reports generated by the IT service teams. Each of the 40 charts will be adjudicated by two reviewers to determine the accuracy of IT reports. We will adjudicate on the primary and secondary outcomes, and key clinical data including mode of nutrition, timing of nutrition, and mode of ventilation. This will operationalize the suitable patient identification for this study, identify any challenges needing to be addressed before embarking on the study in the operations or case report forms and it will help to enhance the validity of our data. Once optimized we will only manually review charts for missing/unclear data.

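### Time from ICU admission to first enteral feed can be derived from the data but is in no covariate list, so a difference in start time between the IEN and CEN groups may be read as a feeding-mode effect

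*Protocol article*

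**What the plan says.** **Covariates.** Table 1 (Statistical Plan) gives the same list for the diarrhea row and the mortality/length-of-stay row: "Age, sex, type of nutrition (IEN/CEN), antibiotics, GI comorbidities, vasopressor/inotropes, daily caloric intake, NIPPV, surgical/trauma/medical admission". The caloric-intake and parenteral-nutrition (PN) row has the same items in another order: "NIPPV, Age, sex, antibiotics, GI comorbidities, type of nutrition (IEN/CEN) vasopressor/inotropes, daily caloric intake, surgical/trauma/medical admission". The bloodstream-infection/*C. difficile* row and the aspiration row have NA in the covariate column and no regression. For infection the method is: "The incidence of bloodstream infections will be computed as the number of new cases during ICU stay divided by the person-time at risk". The Data analysis section adds no timing variable to any of these.

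**Eligibility.** Participants are those "admitted to the ICU for at least 24 hours who have a prescription for EN", or those on non-invasive ventilation (NIPPV) for more than 48 hours. No latest start day for EN is set.

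**Timing of feeding.** The Introduction cites pooled trial evidence of "a reduction in infectious morbidity when EN was delivered within 48 hours of ICU admission". Pilot testing puts timing of nutrition among the items to be checked by two reviewers: "key clinical data including mode of nutrition, timing of nutrition, and mode of ventilation". Under Data collection, mode of nutrition is recorded on each ICU day up to day 30 or ICU discharge.

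**The concern.** In this observational comparison the treating team chose the feeding mode. A patient first fed on ICU day 1 and one first fed on day 10 enter the same IEN/CEN contrast. If one mode tends to be used in patients fed later, the contrast mixes how patients were fed with how soon they were fed.

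The protocol gives reasons to take this seriously. It reports an effect of early EN on infection, which is one of its secondary outcomes. It also treats timing as data important enough to adjudicate, yet does not use it as a covariate. Feeds given after the start cannot change the start day, so adjusting for it does not remove part of the effect of the mode delivered. Daily caloric intake, which is in the lists, is no substitute: it is measured during feeding and may itself depend on mode.

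The outcome windows add to this. Diarrhea counts at any time in the index ICU stay, and blood cultures count from 48 hours after admission. In a late starter, events before the first feed can therefore be credited to a mode not yet begun.

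**Working it through.** **1. The plan's own figure.** Sample size inputs: 25.1% (IEN) and 17.5% (CEN), two-sided alpha 0.05, power 0.80. With the pooled proportion 0.213:

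n = [1.96 × √(2 × 0.213 × 0.787) + 0.842 × √(0.251 × 0.749 + 0.175 × 0.825)]² / 0.076² = 454.4, rounded up to 455 per group.

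This matches the protocol. The present point does not depend on it, but it fixes the planning effect used as a yardstick:
- Risk ratio: 0.251 / 0.175 = 1.43.
- Odds ratio: (0.251/0.749) / (0.175/0.825) = 1.58.
- Risk difference: 7.6 percentage points.

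**2. Spurious risk ratio when mode has no effect.** Let p be the share of a group with late EN (after 48 hours) and RR the effect of late EN on the outcome. The documents give neither, so all values here are assumptions.

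Spurious RR = [1 + p(IEN) × (RR − 1)] / [1 + p(CEN) × (RR − 1)]

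| p(CEN) | p(IEN) | RR of late EN | Spurious IEN/CEN RR |
|---|---|---|---|
| 0.20 | 0.20 | any | 1.00 |
| any | any | 1.0 | 1.00 |
| 0.20 | 0.30 | 1.3 | 1.09 / 1.06 = 1.03 |
| 0.20 | 0.40 | 1.5 | 1.20 / 1.10 = 1.09 |
| 0.20 | 0.50 | 2.0 | 1.50 / 1.20 = 1.25 |

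If IEN is the earlier-started mode, the direction reverses. Exchanging the shares in the last row gives 1 / 1.25 = 0.80.

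**3. The same check on the odds-ratio scale, with other assumptions.** Diarrhea risk with early EN 17.5%, late EN in 30% of CEN and 40% to 60% of IEN, odds ratio for late EN 1.25 to 2.0, no true mode effect.
- Lower end (40%, OR 1.25): crude OR 1.02, risk difference 0.3 points.
- Upper end (60%, OR 2.0): the late-EN risk is 0.298. The IEN risk is 0.6 × 0.298 + 0.4 × 0.175 = 0.249, and the CEN risk is 0.3 × 0.298 + 0.7 × 0.175 = 0.212. Crude OR 1.23, risk difference 3.7 points.

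These are unadjusted contrasts. Covariates already in the models that are related to late feeding would absorb part of the bias.

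**4. Which outcomes are exposed.**
- *Infection, aspiration:* no adjustment is planned. Person-time denominators allow for different lengths of stay, not for early versus late feeding.
- *Diarrhea, mortality:* a covariate list is fixed, and timing is not in it.
- *Length of stay:* the delay is itself part of the outcome. A patient first fed on day 10 has stayed until at least day 10.
- *Caloric intake, PN:* already counted from initiation of CEN/IEN, so the time origin is aligned.

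**The case against.** The strongest reply is that bias needs two things, a difference in start time between groups and an independent effect of start time on the outcome, and the protocol documents neither for its primary outcome. This stands. A reader might infer that timing will distort the IEN/CEN contrast; the documents support only that it may.

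A reader might also infer that the protocol itself says timing changes diarrhea or mortality. It does not. Its 48-hour evidence concerns infection, and its mortality statement is "showed a reduction in mortality with early EN compared to parenteral nutrition (PN"), a comparison with PN and not with later EN. For infection and aspiration the gap is the absence of any adjustment, not one missing covariate.

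Nor is time to first EN a listed variable available for everyone. It must be derived, and it is undefined for NIPPV patients never fed enterally, whom the Participants section includes.

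Three further replies have partial force:
- Vasopressors, GI comorbidities, NIPPV and admission type are plausible reasons for late feeding and are already covariates, and the limitations section concedes confounding in general terms. This may shrink the bias, but it does not adjust for timing itself.
- Group membership depends on mode over most study days, not on the first feed. Start day precedes the first mode used, but not the whole classification. It is a plausible confounder, not a proven one.
- Late starters have by construction survived to their first feed, so the coefficient of delay should not be read causally. Comparing IEN with CEN at equal delay still helps for mortality. For length of stay, entering the delay as a covariate is the wrong remedy.

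Finally, an article may leave detail to a full analysis plan. Here, however, the table headed as the statistical plan states the covariate lists, so this is a written choice.

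**Conclusion.** The point holds as a gap in adjustment, not as a demonstrated bias. Time to first EN is derivable for patients who received EN, the protocol treats timing as key data, and no analysis adjusts for it. The infection and aspiration comparisons, where the protocol's own timing evidence is most relevant, are unadjusted altogether.

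On assumed late-EN shares of 20% in CEN and 20% to 50% in IEN, and a late-EN risk ratio of 1.0 to 2.0, the spurious risk ratio is about 1.0 to 1.25. It is exactly 1.0 if timing is balanced or has no effect. The upper end needs half of IEN patients to start late and a doubling of risk, and even then it is below the planning risk ratio of 1.43, though large enough to affect interpretation. The true size cannot be fixed from the documents.

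**What to change.** Derive time from ICU admission to first EN for patients who received EN, in days or as up to 48 hours versus later. The daily record gives the day; the 48-hour split needs the EN order time or a stated day-based rule. Then:

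- Add it to the Table 1 logistic regressions for diarrhea and for mortality.
- Add it to the Data analysis model of the type of EN chosen. That model would also show whether start time differs between the groups, which is the main unknown here.
- Report the bloodstream-infection and aspiration comparisons by stratum (up to 48 hours, later), or adjusted for it.
- For length of stay, count days from EN start and do not enter the delay as a covariate.
- Leave the caloric-intake and PN models as they are.

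The cost is one derived variable and about one degree of freedom per model, with no new data collection. NIPPV patients never fed enterally drop out of these models, and the plan should say so.

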While guidelines agree on the value of early EN, there is little consensus on how feeds should be delivered [1,4]. Broadly, there are two methods for EN delivery: continuous enteral feeding (CEN), which consists of low rates of tube feeds over a 24-hour period, and bolus/intermittent enteral feeding (IEN), which consists of higher rates of tube feeds delivered over shorter time periods. The American Society of Parenteral and Enteral Nutrition (ASPEN) recommends avoidance of IEN in high-risk patients based on 2 small RCTs which showed a trend towards higher mortality with IEN (13.9% IEN vs 7.4% CEN; p = 0.18) and increased risk of ventilator association pneumonia with IEN (49.3% IEN vs 30.9% CEN, p=0.02) [1,7,8]. However, both trials were published more than 15 years ago. The European Society of Parenteral and Enteral Nutrition (ESPEN) recommends avoidance of IEN in general, citing trends towards worsening diarrhea in 5 small prospective studies [4]. In contrast, 2 meta-analyses, one including 5 RCTs (392 patients) and the other including 9 RCTs (690 patients) have shown no important difference in diarrhea, vomiting, nausea or mortality in patients fed via IEN vs CEN [9,10].

Just as the mode of EN delivery is understudied, so too are the effects of critical illness on the GI tract. Feeding intolerance, diarrhea, vomiting, and ileus are common and associated with increased mortality [11]. While challenging to define, a recent multi-center cohort study found the incidence of diarrhea was as high as 38% with various definitions [12]. Diarrhea has been consistently shown to increase length of stay and contribute to morbidity in ICU patients [11–12,14]. While EN in general has been associated with higher rates of diarrhea [13], the effect of EN strategy (IEN vs CEN) on diarrhea is still unclear. Two recent RCTs including 120 and 112 mechanically ventilated patients respectively found no significant difference in diarrhea, constipation or vomiting [15,16].

Taken together, EN has become the standard of care for most critically ill patients, but little is known about optimal EN strategy or its effect on diarrhea. This is a pragmatic retrospective cohort study that will compare patients receiving IEN and CEN by determining the differences in diarrhea incidence and nutritional exposures, such as the type and volume of EN that patients receive.

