### Data collection

Data will be collected using the search function of EPIC Hyperspace and assistance from HHS and SJHH Information Technology (IT) services teams. The MRN numbers of patients meeting the inclusion criteria will be identified. The data will be exported directly to excel. Any missing data from IT reports will be entered via manual chart review. For each recruited patient, the following baseline characteristics will be recorded to determine factors associated with intolerance of IEN or CEN and with the development of ICU-acquired diarrhea. The baseline characteristics will include demographic data, anthropometric data, clinical data on Day 1 of ICU stay (surgical, medical vs trauma admission, diagnostic category, admitting diagnosis, ventilation status, inotrope/ vasopressor use, renal replacement therapy), admitting hospital, medical comorbidities (prior GI disease, previous luminal surgeries), nutritional assessment (caloric goals on admission will be determined using weight and registered dietician assessment), antibiotic prescription on admission and serum albumin on ICU admission. Table 1 outlines the primary and secondary outcomes as well as the data that will be recorded each day of the ICU admission up until the 30th day or ICU discharge. This includes mode of nutrition (IEN, CEN, oral, or PN), daily caloric intake, mode of ventilation (Invasive, NIPPV), presence of diarrhea, bacteremia greater than 48 hours after admission (gram-positive bacilli and coagulase-negative staph will be reviewed and omitted if team feels it is more likely contaminant), incidence of aspiration pneumonia/pneumonitis, *Clostridioides difficile* infection (CDI), presence of vomiting, ileus or abdominal distention, vasopressor/inotrope dose, average daily insulin dose and blood glucose, survival status in ICU, ICU length of stay. Survival to hospital discharge and hospital length of stay will be collected for the entire hospital stay.

**Table 1 pone.0322122.t001:** Statistical Plan.

Research Objectives	Outcome	Covariates/Subgroups	Analytical Approach
To determine the incidence of diarrhea amongst patients on IEN and CEN	WHO-defined diarrhea	N/A	Descriptive statistics (proportion of patients with diarrhea) and corresponding 95% CI

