### Outcomes

The primary outcome is the incidence of diarrhea defined according to the WHO definition (greater than 3 liquid bowel movements in 24 hours) any time during the index ICU admission (Table 1). This will be identified from nursing flowsheets in EPIC. The secondary outcomes include mortality (ICU and hospital), length of stay (ICU and hospital), incidence of confirmed or suspected hospital-acquired blood stream infections or central line associated blood stream infections, incidence of aspiration pneumonia/pneumonitis (identified pragmatically as documented by the ICU team), CDI, percentage of caloric requirements received by enteral nutrition (daily caloric requirements defined as 25 kcal/kg/day1 and by registered dietician assessment), incidence of vomiting, ileus and abdominal distention, and glycemic control (using average daily insulin dose and average daily glucose as a surrogate) (Table 1).

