### Strengths and limitations

This is a pragmatic study with broad inclusion criteria that should be generalizable to most critically ill patients. It uses the newly implemented EMR at all institutions in Hamilton to generate a large amount of patient data without manual review. It examines two understudied areas of critical care medicine, the effects of EN strategy on diarrhea and the effect of NIPPV on nutrition.

The main weakness in our study is the retrospective strategy. It may be challenging to understand whether differences in diarrhea and daily caloric intake are due to covariates and the severity of illness or the EN strategy chosen. Furthermore, our study centres are all located in Hamilton, Canada; meaning that our findings may be less generalizable to other centres with different practice patterns.

The ENND-GOALs study will generate relevant, pragmatic data regarding EN strategy and diarrhea in the critically ill. Moreover, it will support the findings and inform posthoc analysis from the upcoming INVENTS-ICU RCT, which will also evaluate the differences between IEN and CEN.

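### The Table 1 models for diarrhea and for mortality and length of stay adjust for severity only in part and for comorbidity only through GI disease, so the adjusted IEN/CEN odds ratios cannot be separated from severity of illness

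*Protocol article*

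**What the plan says.** Table 1 gives the same list for the diarrhea risk-factor regression and for the mortality and length-of-stay regression: "Age, sex, type of nutrition (IEN/CEN), antibiotics, GI comorbidities, vasopressor/inotropes, daily caloric intake, NIPPV, surgical/trauma/medical admission". The second of these serves a comparative objective: "To determine whether IEN or CEN is associated with differences in mortality or length of stay (ICU or hospital".

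Data collection records more at admission than these models use. The Day 1 items include "ventilation status, inotrope/ vasopressor use, renal replacement therapy", and the list ends with "antibiotic prescription on admission and serum albumin on ICU admission". Comorbidities are given as "medical comorbidities (prior GI disease, previous luminal surgeries". No composite severity score is named there or in Table 1.

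Two other places bear on the choice of covariates. Strengths and limitations says it may be hard to tell whether differences are "due to covariates and the severity of illness or the EN strategy chosen". The Introduction reports that one guideline body "recommends avoidance of IEN in high-risk patients".

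Data analysis adds two regressions that use baseline characteristics more broadly. One is for reaching caloric targets, the other for which type of EN was chosen. Neither is a model for diarrhea, mortality or length of stay.

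**The concern.** Feeding mode was chosen by clinicians, not allocated. If that choice depends on how sick a patient is, and severity also drives diarrhea, death and length of stay, then the IEN/CEN odds ratio mixes the two unless severity is adequately adjusted for. The article states both the rival explanation and a route by which mode could depend on risk, but the outcome models carry only a few markers of acuity and leave out others that are already being recorded.

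The stake is highest for mortality and length of stay. There the objective is explicitly a comparison of feeding modes, and general comorbidity is an obvious prognostic factor. It is lower for diarrhea: the primary row of Table 1 is descriptive, and the regression is framed as a search for risk factors. Even so, its odds ratio for feeding mode will be reported as adjusted.

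The covariates are written out outcome by outcome. This is a stated specification, not a detail left to an analysis plan that is not shown.

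**Working it through.** **1. What is recorded against what is modelled**

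| Variable | Recorded (Data collection) | In the Table 1 diarrhea and mortality/length-of-stay models |
|---|---|---|
| Vasopressor/inotropes | Yes, Day 1 and daily | Yes |
| NIPPV | Yes, daily ventilation mode | Yes |
| Age, admission type | Yes | Yes |
| Prior GI disease, luminal surgery | Yes | Yes, as GI comorbidities |
| Renal replacement therapy | Yes, Day 1 | No |
| Invasive ventilation | Yes, Day 1 status and daily mode | No |
| Albumin | Yes, at ICU admission | No |
| Composite severity score | Not named | No |
| Non-GI comorbidity | Not named | No |

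Data analysis splits patients into those who did and did not receive NIPPV. If the model term is coded the same way, its reference category pools invasively ventilated patients with those who had no ventilatory support. The NIPPV term then does not stand in for invasive ventilation.

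**2. Does a single acuity proxy suffice?**

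The article gives no association between severity and feeding mode or outcome, so this can only be illustrated. All inputs below are assumptions. Each scenario has 400,000 simulated patients.

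- Severity S is standard normal.
- Vasopressor-type proxy V: logit P(V = 1) = S.
- Feeding mode: logit P(IEN) = logit(0.30) − ln(g)·S, so sicker patients more often get CEN. g = 1.25, 1.5, 2.0 per SD.
- Outcome: logit P(Y) = logit(0.20) + ln(o)·S, with no IEN term, so the true IEN odds ratio is 1. o = 1.25, 1.5, 2.0, 2.5 per SD.

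Because the true odds ratio is 1, a departure from 1 beyond simulation error is confounding, not non-collapsibility.

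| g | o | Crude OR | Adjusted for V | Adjusted for V and S |
|---|---|---|---|---|
| 1.25 | 1.25 | 0.95 | 0.96 | 1.00 |
| 1.5 | 2.0 | 0.77 | 0.80 | 0.99 |
| 2.0 | 2.0 | 0.66 | 0.70 | 0.99 |
| 2.0 | 2.5 | 0.59 | 0.64 | 1.00 |

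Across all 12 scenarios the proxy-adjusted odds ratio runs from 0.96 to 0.64, and the fully adjusted one from 0.99 to 1.01. The share of the log-odds bias removed by the proxy is 1 − ln(adjusted)/ln(crude):

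- 1 − ln 0.80/ln 0.77 = 1 − 0.223/0.261 = 0.15
- 1 − ln 0.70/ln 0.66 = 1 − 0.357/0.416 = 0.14
- 1 − ln 0.64/ln 0.59 = 1 − 0.446/0.528 = 0.15

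The planned models also contain NIPPV, age and admission type, so they may remove more than this one-proxy illustration. The direction was assumed. Reversing it would push the odds ratio above 1, and no link between severity and mode would leave it at 1.

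**3. The plan's own figure**

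The stated 455 per group (25.1% against 17.5%, two-sided 0.05, power 0.8) reproduces with the pooled-variance formula. It does not depend on the covariate list and is not at issue here.

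**The case against.** The strongest reply is that the plan neither ignores severity nor hides the problem. Vasopressor/inotropes, NIPPV, age and admission type are all modelled. The EN-choice regression will show whether mode follows the recorded acuity markers. The limitations paragraph warns the reader. The primary outcome is a pair of proportions with intervals.

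Most of this is correct, and it rules out several stronger readings that a reader might infer:

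- *Severity is not adjusted for at all.* Not so; adjustment is partial.
- *Albumin is used in no model.* The two baseline-characteristics regressions in Data analysis can include it. It is absent only from the outcome models in question.
- *Severity effects will be presented as feeding-mode effects.* The limitations paragraph says the two may be hard to tell apart.
- *Mode follows severity, so the bias has a known direction.* The Introduction also cites a second guideline body that advises against IEN generally, which implies no severity gradient. The Discussion says that local practice and clinician comfort often decide the method.
- *The insulin and glucose comparison mostly reflects diabetes.* The secondary outcome is "glycemic control (using average daily insulin dose and average daily glucose as a surrogate". Nothing in the article suggests that diabetes prevalence differs by feeding mode. The two comorbidities in parentheses may be examples in a condensed article, so it cannot be said that diabetes goes unrecorded.

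What remains is that a caveat does not replace adjusting for markers already recorded. The EN-choice regression can reveal imbalance, but it does not remove imbalance from the outcome models. Whatever the comorbidity parenthesis means, Table 1 models GI comorbidity only.

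**Conclusion.** The point holds in this limited form. The outcome models adjust for severity in part and for comorbidity only through GI disease, while the article itself names severity as the competing explanation and leaves recorded acuity variables unused. The adjusted IEN/CEN odds ratios therefore cannot be separated from severity of illness, and this matters most for mortality and length of stay.

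The size and direction of the residual bias cannot be derived from the documents. The range of 0.96 to 0.64 shows only that, under the assumed associations, one binary proxy can leave anything from a negligible to a substantial bias. It is not an estimate for this cohort. The change is worth making before analysis, but the point does not invalidate the descriptive primary outcome.

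**What to change.** 1. Add Day 1 renal replacement therapy, Day 1 invasive ventilation and admission albumin to the diarrhea and the mortality/length-of-stay models. These are already recorded, so there is no new collection.
2. Where the EMR export allows, extract a Day 1 SOFA-type score and a general comorbidity measure that includes diabetes. Add both to the mortality/length-of-stay model and the score to the diarrhea model. Use diabetes status to describe the insulin and glucose comparison.
3. If a score cannot be extracted, label the IEN/CEN contrasts as descriptive associations and report a sensitivity analysis for unmeasured confounding.

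Cost: a SOFA-type score needs neurological and oxygenation inputs as well as laboratory values. Feasibility says some admission data will need manual review and does not list comorbidity or problem-list data among the confirmed exports. Some missing values and chart review should therefore be expected. The request is cheapest while extraction is open; Timeline gives July 2025 for its completion.

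Degrees of freedom are the other cost. With linear terms and three admission types, the diarrhea model goes from 10 parameters to 13, or 14 with the score. If the expected 500 patients are the total and all are in the comparison, diarrhea events would number about 500 × 0.175 = 88 to 500 × 0.251 = 126, or roughly 6 to 9 per parameter with 14. That is thin, so count the events before the final model is fixed.
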